## Abstract

**Background:**

Diabetes prevalence is rapidly increasing, with type 2 diabetes predicted to be the leading contributor of non-communicable disease in Australia by 2020. It is anticipated that rates of type 2 diabetes will continue to increase if factors such as overweight and obesity, low physical activity and poor nutrition are not addressed. The majority of Australians with type 2 diabetes do not meet the guidelines for optimal diabetes management, and access to diabetes education is limited. This highlights the need for new interventions that can reduce existing barriers to diabetes education, attain greater population reach and support self-management strategies for people with type 2 diabetes.

Mobile phone text messages have shown promising results as an intervention for people with chronic disease. They have the ability to achieve high levels of engagement and broad population reach, whilst requiring minimal resources. There is however, no evidence on the effect of text messaging to improve the health of people with type 2 diabetes in Australia.

**Methods/Design:**

This randomised controlled trial aims to investigate if a 6 month text message intervention (DTEXT) can lead to improvements in glycated haemoglobin (HbA1c) and diabetes self-management among Australian residents in New South Wales (NSW) with type 2 diabetes. Community dwelling adults (*n* = 340) will be recruited with the primary outcome being change in HbA1c at 6 months. Secondary outcomes include behaviour change for diabetes self-management, self-efficacy, quality of life and intervention acceptability. An economic evaluation will be conducted using a funder plus patient perspective.

**Discussion:**

This study will provide evidence on the effectiveness and cost effectiveness of a text message intervention to reduce HbA1c and enhance self-management of type 2 diabetes in the Australian population. If successful, this intervention could be used as a model to complement and extend existing diabetes care in the Australian health care system.

**Trial Registration:**

The study has been registered with the Australian New Zealand Clinical Trials Registry, Trial ID: ACTRN12617000416392. Registered: 23 March 2017.

## Background

Type 2 diabetes is predicted to be the leading contributor to the burden of disease in Australia by 2020 [1]. In 2014–15 it was estimated that one million Australian adults (5%) had type 2 diabetes [2], and if trends continue, this figure could triple to three million by 2025, due to factors such as high rates of overweight and obesity, low physical activity and poor lifestyle behaviours [3]. The majority of Australians with type 2 diabetes do not meet the recommended guidelines for optimum diabetes management [4]. Research shows that diabetes self-management, which includes management of symptoms, treatment, physical and psychosocial consequences, and lifestyle changes [5], can improve glycaemic control and reduce complications in people with type 2 diabetes [6].

Type 2 diabetes, if not managed well, can progress to complications such as coronary artery disease, stroke, kidney failure, limb amputations and blindness [7]. These complications lead to an increased burden of the disease for the health system and the individual [8–11]. By reducing type 2 diabetes related complications, there would be a significant reduction in hospitalisations and the economic burden posed by diabetes on the health care system and people with the disease [12]. Modifiable lifestyle factors such as a poor diet and physical inactivity leading to overweight and obesity are driving the development of type 2 diabetes in the majority of cases [8]. A recent study showed that the majority of Australian adults with type 2 diabetes performed little or no exercise (66%) and had inadequate vegetable (93%) and fruit (51%) consumption [13]. The Australian Institute of Health and Welfare (AIHW) reported that only 55% of Australians with type 2 diabetes effectively manage their condition, and this figure reduces to 38% for Indigenous adults [14]. The AIHW also reported that only 18% of Australian’s complete the Annual Cycle of Care [13], the recommended best practice for the management of type 2 diabetes [7].

International studies suggest that attendance at diabetes education sessions can be as low as 30% due to logistical, medical, or financial reasons; or a perceived lack of benefit [15]. In Australia, it has been reported that over 40% of people with type 2 diabetes have no access to diabetes education programs [16], and only 24% of people saw a diabetes educator in the last year [14]. A study of Australian adults aged 18–39 years with type 2 diabetes showed that 59% chose not to participate in a structured education program with the perception that programs do not cater to their needs or concerns [17]. People not attending diabetes education have a fourfold increased risk of complications [18], therefore self-management of type 2 diabetes is critical to delaying or preventing disease progression and complications [19–21].

The use of mobile phone text message interventions to complement existing health care is a rapidly emerging field [22–24]. Text message interventions have the potential for high population reach; require minimal resources; and can be easily translated into the routine practice and existing services. In Australia, 96% of adults use a mobile phone [25], and it has been shown that usage is high amongst people from lower socioeconomic areas, rural and remote regions, the aging population and those with higher body mass index, health comprising behaviours and lower levels of self-rated health [26–29]. These socio-demographic characteristics align closely with those having a higher prevalence of type 2 diabetes [30], suggesting that a text message intervention could be an appropriate method to support self-management of their condition.

Research has shown that text message interventions can improve the short term health of cardiac patients [31], help promote smoking cessation [32] and assist in weight loss [29] by providing prompts, information, reminders and support. Studies have also shown that text messaging can aid in lowering blood pressure [33], and improve medication adherence [34], physical activity [35], weight loss [36] and glycaemic control [24, 37, 38], however, these studies have been limited due to factors such as a short study duration, small sample size and lack of theoretical basis [39–42].

A recent systematic review and meta-analysis by Faruque et al. 2017 for people with type 1 and 2 diabetes showed that text messaging interventions resulted in some improvement in glycaemic control, but not other clinical outcomes [43]. A systematic review by Dobson et al. 2017 reported that improvements in glycaemic control from text message interventions were inconclusive for people with sub optimal (HbA1c 7.1–8%) or poorly controlled diabetes (HbA1c ≥8.1%) [22]. Currently no evidence exists for a text message intervention to improve the health and support self-management of adults with type 2 diabetes in Australia.

## Aim

This study aims to determine the effectiveness and cost effectiveness of a text message intervention (DTEXT) on improvements in glycated haemoglobin (HbA1c) and self-management for people with type 2 diabetes.

## Methods

### Design

This study protocol describes a 6-month text message intervention (DTEXT) that will be conducted as a randomised controlled trial, with two parallel arms, an intervention arm and a control arm - see Fig. 1.

**Fig. 1 Fig1:**
[figure not shown]
Study design and flow. HbA1c: glycated haemoglobin, MBS: Medicare Benefits Schedule, PBS: Pharmaceutical Benefits Scheme

The study protocol is in accordance with the SPIRIT 2013 statement [44], the Consolidated Standards of Reporting (CONSORT) – eHEALTH checklist [45] and Hoffman et al’s 2014 [46] extension of these two documents.

### Participants

Participants will be community dwelling adults with a diagnosis of type 2 diabetes and an HbA1c of 7% (53 mmol/mol) or above, who reside in New South Wales, Australia. Participants must be 18 years or older, own and be able to use a mobile phone, be able to read and speak English, and be able to provide informed consent. Exclusion criterion is pregnancy, to exclude gestational diabetes.

### Recruitment

Participants will be recruited by referral from health service providers and doctors; advertising in newspapers, community noticeboards, radio and social media (Facebook); and mail outs through the regional public health Diabetes and Renal Services in the Illawarra Shoalhaven Local Health District, and the Australian Government National Diabetes Services Scheme.

### Sample size

The required sample size of 340 (170 per arm) will provide 80% power of detecting a between-group change in HbA1c of 0.7%, allowing for 20% loss to follow up and an alpha = 0.05.

### Randomisation and blinding

The PROC PLAN function in Statistical Analysis System (SAS) v 9.4 will be used to randomise participants into sets of two letters (A and B, representing the intervention and control arms respectively) by blocks of four to ensure a balanced sample size across both study groups. Couples will be treated as a single unit to ensure both are allocated to the same treatment group.

The randomisation letters will be generated by a statistician at the University of Sydney, and packaged by a NSW Health staff member not involved in the study to ensure group allocation is concealed from the researcher until completion of baseline measures.

Participants will be randomised into the intervention or control arm after providing informed consent, obtaining medical clearance and completing baseline measures. Due to the nature of the intervention and telephone surveys conducted, participants and researchers cannot be blinded to treatment allocation. Pathology collectors assessing objective measures (HbA1c, lipids, height and weight) and the participant’s doctor will not be informed of treatment allocation.

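### A single disclosed block size of four, with researchers unblinded after each allocation, lets up to a third of allocations be foreseen and weakens concealment

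*Protocol article*

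**What the plan says.** All of the randomisation text is in the Protocol article, Randomisation and blinding.

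- **Block size.** Allocation is "by blocks of four to ensure a balanced sample size across both study groups". Varying sizes and stratification are not mentioned, and nothing says that the block size is kept from the study staff.
- **Code.** The letters are "A and B, representing the intervention and control arms respectively", so a released letter identifies the arm.
- **Concealment.** A university statistician generates the letters, and a health-service employee from outside the trial packages them, "to ensure group allocation is concealed from the researcher until completion of baseline measures".
- **Order of events.** "Participants will be randomised into the intervention or control arm after providing informed consent, obtaining medical clearance and completing baseline measures".
- **Blinding.** "participants and researchers cannot be blinded to treatment allocation". The pathology collectors and the participant's doctor are not told the allocation.
- **Unit.** "Couples will be treated as a single unit to ensure both are allocated to the same treatment group".

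Under Secondary outcomes, the research team administers the telephone questionnaire at baseline, 3 and 6 months.

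**The concern.** Outside packaging hides a letter that has not yet been opened. It does not stop that letter being deduced from letters already opened in the same block. With blocks of four, once one arm has been used twice within a block, every remaining place in that block is known. Researchers learn each allocation after baseline, and the block size is printed in the trial's own protocol article. The information needed for the deduction is therefore within reach of the people whom the concealment is meant to cover.

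A staff member who foresees the next allocation could, knowingly or not, affect whether or when a person becomes ready for randomisation, or how a baseline interview is conducted. Selection at entry can reach any outcome, including HbA1c. An influenced interview can affect the self-reported measures, whose models are adjusted for baseline scores (Statistical analysis). Because the participants and researchers are unblinded, concealment up to the point of allocation matters more here than in a masked trial.

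**Working it through.** The plan gives no predictability figure to reproduce. The inputs taken from it are two arms in equal numbers (170 + 170 = 340, Sample size) and a block size of four (Randomisation and blinding). 340 / 4 = 85 complete blocks if every unit is one person.

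**Step 1. Allocations known with certainty.** A position is forced when one of the letters in its block has been used up. The six possible blocks are equally likely:

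| Block | Forced positions | Count |
|---|---|---|
| AABB | 3, 4 | 2 |
| BBAA | 3, 4 | 2 |
| ABAB | 4 | 1 |
| ABBA | 4 | 1 |
| BAAB | 4 | 1 |
| BABA | 4 | 1 |

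Total forced: 2×2 + 4×1 = 8 of 6×4 = 24 positions, or 33.3%. The fourth place is always forced. The third is forced one time in three, when the first two letters of the block are the same. Two identical letters in a row elsewhere in the list do not have this effect.

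**Step 2. In numbers of participants.** 85 blocks × 4/3 = 113.3, so about 113 of 340. This is the average for an observer who tracks the list without error. With *c* couples enrolled among 340 people there are 340 − *c* units, and the figure becomes about (340 − *c*)/3. The document does not give *c*.

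**Step 3. Best-guess success.** The observer guesses the arm with more letters left in the block, and tosses a coin when they are equal. The chance of being right is 1/2 at place 1 and 2/3 at place 2. At place 3 it is 1/3×1 + 2/3×1/2 = 2/3, and at place 4 it is 1. The sum is 17/6 per block, and (17/6)/4 = 17/24 = 70.8%, against 50% under simple randomisation.

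**Step 4. Alternatives.** Fixed blocks were enumerated in the same way. Random blocks were simulated with 1,000 lists of 340, for an observer who knows the set of sizes but not their order and updates after each letter.

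| Scheme | Known with certainty | Best guess correct |
|---|---|---|
| Fixed 4 (the plan) | 33.3% | 70.8% |
| Fixed 6 | 25.0% | 68.3% |
| Fixed 8 | 20.0% | 66.6% |
| Random 4/6, order hidden | about 5.4% | about 69.3% |
| Random 4/6/8, order hidden | about 2.2% | about 68.1% |

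For 340 units, 2.2% is about 8 allocations (0.0224 × 340 = 7.6), against about 113. The gain is almost wholly in certainty, because a long-run tendency to balance remains guessable under any small-block scheme.

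**The case against.** The strongest defence is that the plan does set up real concealment: generation by a statistician, packaging by someone outside the study, and release only after baseline. Two thirds of allocations are not determined in advance even for a perfect observer. Eligibility is mostly objective (Participants), and medical clearance and local blood tests put part of the timing in other hands. The primary outcome is a blood test handled by collectors who are not told the allocation.

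Most of this stands, and it limits the point. A reader might infer that concealment is defeated, or that one unblinded team takes referrals, enrols, allocates and follows up. The document supports neither. It says that researchers are unblinded and that the research team gives the questionnaire, but not who receives referrals or whether interviewers see the running sequence. A reader might also take 113 as a count of allocations actually known. It requires someone who knows the block size, knows where blocks begin and has every earlier allocation in order. A tally kept by person goes out of step once a couple is entered as one unit.

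The defence does not remove the weakness. Blinded collectors protect how HbA1c is measured, not who is entered or in what order. Objective eligibility criteria do not fix the time at which a person's baseline is completed. Adjustment for baseline scores can address measured imbalance, but not unmeasured selection or a baseline interview that was itself influenced. The block size is a stated choice, not a detail left out by condensing a longer protocol.

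**Conclusion.** The point holds in a limited form. One block size of four, disclosed in the article and used where researchers learn each allocation, allows up to one third of allocations to be foreseen with certainty: at most about 113 of 340, and fewer with couples. Concealment is undermined for that share and weakened for some others, but not removed.

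The risk is to the selection or timing of entry and to self-reported baseline data, and analysis can correct it only in part. Measurement of HbA1c is not at issue.

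The size rests on three assumptions: a single list (no stratification is described), an observer who knows the block size, and a correctly tracked sequence. The document makes these plausible but does not establish that anyone would track or use the sequence. The reason to act is that the weakness is avoidable at almost no cost.

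**What to change.** The university statistician should generate the list in the same SAS procedure with randomly varying block sizes, for example 4, 6 and 8. The sizes and their order should be withheld from enrolling and interviewing staff, and from documents they see, until recruitment ends. If recruitment has begun, apply this to the unused part of the list.

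The expected gain is a fall in allocations known with certainty from 33% to about 2%. The change should not be presented as removing guessability, since best-guess success moves only from about 71% to about 68%.

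The cost is a few lines of code. If recruitment stops inside a block of eight, the arms can differ by up to four units (half the block), which is negligible at 340. The aim of balanced arms is still met.

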### Statistical analysis

Statistical analysis will be conducted using the software programs Statistical Package for the Social Sciences (SPSS-25) and Statistical Analysis System (SAS) v9.4, with an intention to treat principle.

Generalised estimating equation (GEE) models will be used to assess impact, modelling repeated outcome measures over time. Change in HbA1c will be analysed using GEE models to test the effect of the intervention on change in HbA1c between the two groups.

GEE will also be used to assess the effect of group allocation on changes over time in BMI, TC, LDL-C, HDL-C, TG, physical activity, dietary behaviour, smoking status, quality of life, self-efficacy measures and use of health services after adjusting for baseline scores. Two planned subgroup analyses will be undertaken to assess differential impact of the intervention on the basis of age and sex.

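### Couples are randomised as one unit, but the analysis text does not carry that unit into the GEE; naming it as the cluster would remove a small avoidable error

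*Protocol article*

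**What the plan says.** Three sections of the Protocol article bear on this, and a fourth is affected.

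- **Randomisation and blinding.** Allocation is to two arms in blocks of four, with one exception to individual randomisation: "Couples will be treated as a single unit to ensure both are allocated to the same treatment group".
- **Statistical analysis.** "Generalised estimating equation (GEE) models will be used to assess impact, modelling repeated outcome measures over time". The section then applies GEE to change in HbA1c and to the secondary outcomes. It does not name the cluster (subject) identifier, the working correlation or the variance estimator, and it does not mention couples.
- **Sample size.** "The required sample size of 340 (170 per arm) will provide 80% power", for a between-group HbA1c difference of 0.7%, "allowing for 20% loss to follow up and an alpha = 0.05". No standard deviation, design effect or share of couples is given.
- **Economic evaluation.** Bootstrapped cost and outcome estimates are planned. The unit to be resampled is not named.

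**The concern.** For participants who enrol as a couple, this is a cluster-randomised trial with clusters of two. Robust GEE standard errors are valid when each cluster holds all the observations that are correlated with one another. If the person is the cluster, the correlation among one participant's visits is covered but the correlation between partners is not.

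Partners may well respond alike, because the messages address eating, physical activity, weight and smoking, which are often shared in a household. With positive within-couple correlation, the variance of the treatment effect is understated, confidence intervals are too narrow, and the test rejects somewhat more often than its nominal level. The same would hold for the cost-effectiveness plane and acceptability curve if the bootstrap drew individuals and split couples.

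**Working it through.** **1. The plan's own figure.** 340 cannot be reproduced, because no SD is given. It can only be solved backwards.

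- Evaluable per arm: 170 × (1 − 0.20) = 136.
- Two-sided alpha 0.05 (sidedness is not stated; this is an assumption), power 80%, difference 0.7.
- SD = 0.7 / [(1.960 + 0.842) × √(2/136)] ≈ 2.06.

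So 340 fits a two-sample calculation without a design effect if the SD was about 2.06. It also fits other bases. With an SD of 2.0, 129 evaluable per arm are enough (162 per arm after 20% loss, 324 in total), and the 136 evaluable per arm would leave room for a design effect of 136/129 ≈ 1.05. The total of 340 therefore does not show whether couples were allowed for.

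**2. Design effect.** Let f be the share of participants enrolled as part of a couple and ρ the within-couple correlation of the outcome analysed. Among n participants in an arm, f·n have a partner in the same arm, so the variance of the arm mean is

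(σ²/n) × (1 + f·ρ), giving DE = 1 + f·ρ.

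**3. Consequence if partners are treated as independent.** The standard error is too small by a factor √DE, and

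type I error = 2 × [1 − Φ(1.96/√DE)].

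Both f and ρ are assumptions; the article gives neither.

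| f | ρ | DE | √DE | True type I error | Power if 340 had no allowance and SD = 2.06 |
|---|---|---|---|---|---|
| 5% | 0.1 | 1.005 | 1.002 | 5.1% | 79.8% |
| 10% | 0.3 | 1.03 | 1.015 | 5.4% | 78.8% |
| 20% | 0.3 | 1.06 | 1.030 | 5.7% | 77.7% |
| 20% | 0.5 | 1.10 | 1.049 | 6.2% | 76.2% |

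The last column is conditional on the back-solved SD and on there having been no allowance for couples. It shows scale only and is not evidence that the stated power is wrong.

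**4. Which correlation matters.** The primary comparison is of change in HbA1c, and the secondary models adjust for baseline. The relevant ρ is therefore the correlation between partners in change, or in outcome given baseline. A stable household similarity that is already present at baseline largely cancels, so ρ may be lower than the similarity in levels would suggest.

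**The case against.** The strongest objection is that the article does not say the person is the cluster. A GEE clustered on the couple also models repeated measurements, and would fit the Statistical analysis text. The identifier is a detail that a condensed article commonly leaves to a fuller protocol or an SAP, and neither is shown. This stands: a reader might infer that the plan has fixed the wrong cluster, but the text supports only that it names one source of dependence and leaves out another that its own randomisation section created.

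A reader might also infer that the sample size counts 340 independent allocations and that the 80% power is overstated. The Sample size section gives no SD or calculation basis, so this may be true but cannot be shown.

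A third tempting reading is that the error always runs in the anti-conservative direction. It does so only when the within-couple correlation is positive, which is plausible but not documented.

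Finally, the share of couples may be low, because both partners must have type 2 diabetes with HbA1c of at least 7% and both must enrol. This argues against the top of the assumed range, although the article gives no figure and sets no cap on couples.

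What the objection does not remove is that the randomised unit is stated and the analysis description does not take it up. An analyst working from that description would ordinarily use the participant identifier.

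**Conclusion.** The point holds as a minor one, with moderate confidence. The randomisation section makes the couple a unit of allocation, and the analysis section does not follow it through. If the GEE is run with the person as cluster, the type I error of a nominal 5% test is about 5.1% to 6.2%, and standard errors are understated by a factor of 1.002 to 1.049. These ranges rest on an assumed 5% to 20% of participants in couples and an assumed positive within-couple correlation of 0.1 to 0.5; the upper end needs both at their maximum. The trial is not invalidated, and the documents do not support a claim that its stated power is wrong. The reason to act is that the remedy costs almost nothing and makes the analysis match the randomisation.

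**What to change.** - In the Statistical analysis section (or the SAP, if it does not already say so), define the GEE cluster as the randomised unit: a couple identifier for partners and the participant's own identifier for everyone else, with visits nested within person within unit and robust standard errors. A couple then contributes up to six HbA1c records (two people at three visits), so the working correlation must accommodate that.
- In the Economic evaluation section, state that the bootstrap resamples the same unit, keeping both partners together.

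The cost is one identifier in the data set and the code, and a sentence in each section. Confidence intervals may become slightly wider, by up to about 5% at the top of the assumed range (√1.10 ≈ 1.049). No change in sample size is needed.
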